### 3.6. Expected Outcomes

Results will be reported in accordance with the CONSORT 2010 guidelines.

The primary outcome will be reported as the change from baseline to post-intervention in MOXO CPT total score, presented as estimated marginal means with standard errors for each group, along with 95% confidence intervals and effect sizes (Cohen’s d). It is anticipated that participants in the Sincrolab Adults group will show greater improvement compared to the control group.

Secondary outcomes (e.g., ASRS scores) will be reported as mean changes, proportions of participants achieving clinically significant improvement (defined as a reduction of 12 points or more on ASRS), and corresponding odds ratios and confidence intervals. It is expected that the Sincrolab Adults group will exhibit a greater reduction in ASRS score and a higher proportion of participants achieving a clinically significant improvement compared to the control group.

Exploratory outcomes (AAQoL scores, additional MOXO indices) will be presented as mean (±standard deviation) pre–post changes for each group, along with group × time interaction *p*-values and effect sizes for each exploratory measure. Participants in Sincrolab Adults are expected to show greater pre–post gains in quality of life and MOXO sub-indices compared with controls. We anticipate positive correlations between improvements in CPT indices and improvements in functional outcomes (ASRS) and quality of life (AAQoL). Finally, we expect treatment benefits to be maintained at the 1-month follow-up.

## 4. Discussion

This study describes a clinical trial designed to evaluate the efficacy of Sincrolab Adults, an AI-based cognitive training intervention tailored for adults with ADHD (inattentive or combined presentation). While pharmacological treatments remain the standard of care, many adults with ADHD do not respond adequately to medication or discontinue due to side effects. Cognitive training offers a promising, non-pharmacological alternative, yet evidence supporting its effectiveness in adults remains limited. This study aims to address this gap in the literature.

Digital cognitive training is theoretically grounded in the concept of experience-dependent neuroplasticity [41], whereby repeated, adaptive cognitive challenges strengthen neural circuits involved in attention, working memory, and inhibition—core deficits in ADHD. Adaptive training that dynamically adjusts task difficulty may enhance engagement and target individual cognitive limitations more effectively than fixed protocols. Improvements in these cognitive domains (i.e., near-transfer effects) may translate into better performance on tasks like the MOXO-CPT, which relies on sustained attention, impulse control, and processing speed. Additionally, gains in these areas may produce far-transfer effects, such as reductions in daily ADHD symptoms (ASRS) and improvements in quality of life (AAQoL). However, such generalization remains a matter of empirical debate [16,23].

This study may also provide insight into the broader accessibility and public health potential of online cognitive interventions. Digital platforms like Sincrolab Adults have the capacity to overcome geographical, economic, and logistical barriers that limit access to conventional, face-to-face therapies. For individuals from underserved or socioeconomically disadvantaged backgrounds, these tools could offer a scalable and cost-effective alternative, particularly in regions with limited access to adult ADHD specialists. However, issues of digital equity remain an important consideration. Future research should examine how factors such as internet access, digital literacy, and cultural context influence engagement and uptake across diverse populations.

It is also important to consider that observed improvements on performance-based tasks may be influenced by practice effects, and changes in self-reported outcomes could partly reflect expectancy biases, especially given the use of a treatment-as-usual control rather than an active placebo. While outcome assessors and data analysts are blinded to group allocation to reduce detection and analysis bias, participants are aware of their assignment, which may affect subjective reporting. These limitations will be carefully considered when interpreting the findings and will be addressed through sensitivity analyses where appropriate.

Additionally, this trial will explore potential moderators such as ADHD subtype (inattentive vs. combined), medication status, adherence to training, and use intensity. These variables may help identify individuals most likely to benefit from cognitive training. The inclusion of a 1-month follow-up will also provide preliminary insight into the durability of treatment effects, which remains a critical issue in digital health interventions.

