where:z_α/2_: Critical value for the significance level (α = 0.05) = 1.96.zβ: Critical value for power (1 − β = 0.801) = 0.84.d: Effect size (d = 0.62).n: Sample size per group.

The study protocol (Figure 1) will span 12 weeks plus an additional month of follow-up, with three assessments (baseline, post-intervention, and follow-up). Participants in the intervention group will use a digital cognitive training program designed to target multiple cognitive functions associated with ADHD dysfunctions. The program will include adaptive training games that can be played on a computer or mobile device. Participants will play the training games 3 to 5 times per week, for 15 min per session, over a 12-week period. Participants in the control group will not receive the intervention during the 12-week trial but will be offered access to the program after the study concludes.

The study flow diagram is as follows:

Inclusion criteria.

Participants must meet all of the following:○Adults aged 18 and older○Clinical diagnosis of ADHD according to DSM-5 criteria, confirmed using the DIVA 5.0 Interview for Attention-Deficit/Hyperactivity Disorders Studies (Adult version)○Stable use or non-use of ADHD medications for at least 2 weeks prior to enrollment and throughout the 12-week study period○Baseline ADHD-RS score ≥ 28○Ability to understand and follow written and verbal instructions in Spanish, as assessed by the Principal Investigator or study coordinator○Completion of the informed consent form○Access to a compatible digital device○Willingness and ability to comply with all study procedures and testing requirements

Exclusion criteria.

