### 4.2. Limitations and Future Directions

Despite its strengths, the study also presents several limitations that should be acknowledged. One notable limitation is the relatively short follow-up period and the limited number of measurement points. While additional assessments during the intervention period could provide a more granular understanding of treatment effects over time, the practical challenges associated with repeated testing in adults with ADHD, such as inattention, restlessness, and difficulties with sustained engagement, necessitate a parsimonious approach. To maximize participant retention in follow-up assessments, reminders will be systematically sent, and study personnel will actively reach out to non-responders.

Another potential challenge is participant attrition throughout the intervention. Given the well-documented executive functioning difficulties in ADHD, dropout rates may be higher than those observed in other clinical populations. To mitigate this risk, participants who fail to complete training modules will receive weekly follow-ups, along with technical and motivational support as needed.

Furthermore, although adherence metrics (e.g., the number of completed training sessions and total time spent on tasks) will be monitored, an inherent limitation remains in quantifying the quality of engagement during training sessions. While adherence data provide a proxy for treatment exposure, they do not capture variability in motivation, attentional effort, or strategy use, which may influence outcomes. Future studies may benefit from incorporating real-time monitoring or behavioral analytics to assess engagement quality more precisely.

Importantly, while outcome assessors will be blinded to group allocation, participants themselves will not, due to the nature of the intervention. This introduces the possibility that expectancy effects could influence self-reported outcomes. Additionally, although the use of a control group is ethically and practically appropriate, it does not account for placebo effects or the influence of structured engagement, factors that may contribute to observed improvement.

Finally, since the study will be conducted within a specific healthcare and cultural context, the generalizability of findings may not be fully generalizable to other populations or health systems.

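### Adherence to training and use intensity are listed as moderators, but they arise after randomisation and only in the intervention arm, so they cannot show who benefits

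*Protocol article*

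**What the plan says.** Section 4 (Discussion) announces that "this trial will explore potential moderators such as ADHD subtype (inattentive vs. combined), medication status, adherence to training, and use intensity". The next sentence gives the purpose: "These variables may help identify individuals most likely to benefit from cognitive training".

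Two other sections fix what adherence and use can mean in this trial:

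- Section 3.1: "Participants in the control group will not receive the intervention during the 12-week trial". For the intervention arm, "Participants will play the training games 3 to 5 times per week, for 15 min per session, over a 12-week period".
- Section 4.2: adherence is measured by completed sessions and time on tasks, logged as training proceeds. The section adds that "adherence data provide a proxy for treatment exposure", but that "they do not capture variability in motivation, attentional effort, or strategy use, which may influence outcomes".

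Section 3.5 builds the primary model from group, time, their interaction, a random intercept and demographic covariates. It has no adherence term. The objectives in Section 2 and the expected outcomes in Section 3.6 do not mention moderators.

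**The concern.** A variable can show who benefits more from a treatment if it is fixed before randomisation and observed in both arms, so that the treated-versus-control difference can be compared across its levels. ADHD subtype and medication status meet that requirement. Adherence to training and use intensity do not: they are consequences of being assigned to train, and controls have nothing to adhere to.

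Setting all four side by side under one stated purpose invites the same reading for each. If heavy users improve more than light users, a reader would take it that heavy users benefit more. The pattern could equally arise because people who keep up a training schedule would have improved more in any case. The article itself gives reason to expect this. Section 4.2 names motivation and attentional effort as possible influences on outcome and links executive difficulties to dropout. Section 4 says that the MOXO test relies on sustained attention and impulse control. The traits that limit training use therefore overlap with those that the primary outcome measures.

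**Working it through.** **1. The plan's own figure.** The sample size in Section 3.1 reproduces and is not in dispute.

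- n per group = 2 × (1.96 + 0.84)² / 0.62² = 15.68 / 0.3844 = 40.79, rounded up to 41.
- With 20% dropout: 41 / 0.8 = 51.25, rounded up to 52 per group, 104 in total.

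The illustration below uses 41, the number of intervention participants expected to be evaluable.

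**2. Can an arm × adherence interaction be estimated?** Let g be arm (0 control, 1 intervention) and a be adherence. A moderator model needs the columns 1, g, a and g × a.

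- If a is set to 0 for controls, then g × a = a for every participant: both are 0 in controls and both equal a in the intervention arm. Two columns are identical. A numerical check with 52 per arm gives rank 3 for the four columns.
- If a is treated as missing for controls, they drop out and no comparison with control remains.

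Either way, only the slope of outcome on adherence within the intervention arm is left, and randomisation does not protect that slope. The same holds for use intensity.

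**3. How misleading could the within-arm slope be?** The documents give no correlation, so this step rests on assumptions and is shown as a range. Suppose training has no effect, and one unmeasured trait has correlation k with adherence and the same correlation k with outcome change. The adherence–outcome correlation is then r = k². With n = 41, the Fisher transformation gives a mean test statistic m = arctanh(r) × √(n − 3) = arctanh(r) × √38, and the two-sided rejection rate at 0.05 is Φ(m − 1.96) + Φ(−m − 1.96).

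| k (assumed) | r = k² | m | Trials significant at 0.05 |
|---|---|---|---|
| 0.2 | 0.04 | 0.25 | 6% |
| 0.3 | 0.09 | 0.56 | 9% |
| 0.4 | 0.16 | 0.99 | 17% |
| 0.5 | 0.25 | 1.57 | 35% |

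Simulation of the same set-up (40,000 trials per row) agrees to within one percentage point in each row.

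The expected gap in outcome change between the more and less adherent halves is about 2 × √(2/π) × r = 1.596r. At k = 0.5 this is 1.596 × 0.25 = 0.40 SD, and at k = 0.2 it is 1.596 × 0.04 = 0.06 SD. The trial is designed to detect 0.62 SD. Adding the same benefit for every participant would shift both halves equally and leave these figures unchanged.

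**The case against.** The strongest reply is that the article commits to very little. The wording is hedged, appears only in the Discussion, and states no arm × adherence model. A condensed article may leave the method to an analysis plan that is not shown. Section 4.2 already concedes that usage logs miss motivation. The size of the distortion also depends wholly on the assumed correlations and is close to nominal at the low end of the range.

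Much of this stands. Three stronger readings are tempting, and the documents do not support them:

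- *That the plan asserts these variables identify who benefits.* It says only that they may help to do so.
- *That a dose–response would be reported as the treatment effect.* The effect is estimated from the randomised group × time comparison (Section 3.5) and reported as change by group (Section 3.6). Nothing says that an adherence association would replace or support it.
- *That the false-positive rate is seven times nominal.* That is the single assumed point k = 0.5 (35% against 5%). At k = 0.3 it is under twice nominal.

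The classification itself does not survive the reply. No analysis plan can turn adherence into a baseline variable present in both arms. The remark on motivation in Section 4.2 concerns how well engagement is measured, and it does not withdraw the inference in Section 4.

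**Conclusion.** The point holds for two of the four listed variables. Adherence to training and use intensity are measured after randomisation and exist only in the intervention arm. Their interaction with arm cannot be estimated, and a within-arm association cannot separate an effect of dose from motivation and prognosis. They therefore cannot show who benefits. This conclusion follows from the design and needs no numerical assumption.

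The size of any distortion is uncertain. The range of 6% to 35% rests on an assumed single trait, equal correlations of 0.2 to 0.5, 41 participants and no training effect.

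The severity is minor. The analysis is exploratory, and the primary analysis, the sample size of 104 and the two baseline moderators are untouched.

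**What to change.** 1. In Section 4, limit the term moderator to baseline variables, for example ADHD presentation, medication status, age and baseline MOXO score, each tested as an arm × time × variable term.
2. Report adherence and use intensity as descriptive associations within the intervention arm.
3. Reword the sentence on identifying those most likely to benefit so that it no longer covers these two variables.

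This costs a few words and changes no stated figure.

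A complier-average analysis, with randomised arm as the instrument and a preset number of completed sessions as compliance, is optional. It would use logs already planned, but it answers a different question: the effect among compliers, not who benefits. It also needs the exclusion restriction to be stated, namely that assignment has no effect on people below the session threshold. Partial training, expectancy in unblinded participants and the weekly motivational support for those who miss modules (Section 4.2) all threaten that assumption, and the interval is likely to be wide. Relabelling is sufficient without it.

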### 4.1. Strengths

One of the primary strengths of this study is its personalized, adaptive treatment approach. Sincrolab Adults utilizes a series of adaptive cognitive training games that dynamically adjust to match each participant’s individual cognitive profile. This level of personalization is expected to enhance engagement and treatment adherence, potentially leading to greater efficacy than conventional, non-adaptive interventions.

A key strength of this study is the single-blind design, in which both outcome assessors and data analysts are blinded. This approach minimizes detection and analysis bias, enhancing the reliability and validity of objective cognitive and functional outcomes. Although patients are aware of their group assignment and placebo or performance effects cannot be fully controlled, the design ensures robust assessment of treatment effects while maintaining internal validity. Additionally, the research team, including Sincrolab, has extensive experience in digital therapeutics (DTx) research and ADHD clinical studies, ensuring high methodological rigor in recruitment, treatment delivery, data collection, and analysis. The expertise of the investigators and the established research infrastructure contribute to the feasibility and successful execution of this trial.

### 4.2. Limitations and Future Directions

Despite its strengths, the study also presents several limitations that should be acknowledged. One notable limitation is the relatively short follow-up period and the limited number of measurement points. While additional assessments during the intervention period could provide a more granular understanding of treatment effects over time, the practical challenges associated with repeated testing in adults with ADHD, such as inattention, restlessness, and difficulties with sustained engagement, necessitate a parsimonious approach. To maximize participant retention in follow-up assessments, reminders will be systematically sent, and study personnel will actively reach out to non-responders.

Another potential challenge is participant attrition throughout the intervention. Given the well-documented executive functioning difficulties in ADHD, dropout rates may be higher than those observed in other clinical populations. To mitigate this risk, participants who fail to complete training modules will receive weekly follow-ups, along with technical and motivational support as needed.

Furthermore, although adherence metrics (e.g., the number of completed training sessions and total time spent on tasks) will be monitored, an inherent limitation remains in quantifying the quality of engagement during training sessions. While adherence data provide a proxy for treatment exposure, they do not capture variability in motivation, attentional effort, or strategy use, which may influence outcomes. Future studies may benefit from incorporating real-time monitoring or behavioral analytics to assess engagement quality more precisely.

Importantly, while outcome assessors will be blinded to group allocation, participants themselves will not, due to the nature of the intervention. This introduces the possibility that expectancy effects could influence self-reported outcomes. Additionally, although the use of a control group is ethically and practically appropriate, it does not account for placebo effects or the influence of structured engagement, factors that may contribute to observed improvement.

Finally, since the study will be conducted within a specific healthcare and cultural context, the generalizability of findings may not be fully generalizable to other populations or health systems.

Future research should consider the inclusion of active control groups (e.g., sham training or non-specific digital tasks) to better isolate the specific effects of cognitive stimulation. Studies with longer-term follow-up and more frequent assessments would provide greater insight into treatment durability and the timing of clinical response. Additionally, expanding recruitment to more diverse settings and populations would enhance the external validity of the findings. Finally, incorporating objective measures of engagement and behavioral responses may help clarify the mechanisms underlying individual differences in treatment outcomes.

## 5. Conclusions

Despite these limitations, this study has the potential to make a meaningful contribution to the field of ADHD treatment by evaluating a digital cognitive training intervention with a rigorous, controlled methodology. Given the limited availability of validated non-pharmacological treatments for adults with ADHD, this research could help address a critical gap in care. If successful, the findings could support the broader implementation and dissemination of digital therapeutics for ADHD, ultimately expanding access to evidence-based interventions for individuals who may not respond adequately to medication. Future studies should focus on refining digital cognitive training approaches, assessing longer-term outcomes, and exploring how these interventions can be applied in real-world clinical settings across diverse populations.

## Figures and Tables

**Figure 1 jcm-14-06629-f001:**
[figure not shown]
Study design showing participant flow, randomization, intervention with cognitive stimulation software, control group, and assessment time points.

## Data Availability

No data are available at this time. Data will be published and shared upon request once available.
